#### Participant timeline

Figure 1 describes the flow of potential participants in the trial.

**Fig. 1 Fig1:**
[figure not shown]
Flow of participants through the trial

### Outcomes

All outcomes will be measured at 1–2 weeks prior to the intervention, 1–2 weeks after the intervention, and 3 months after the intervention has concluded (Table 2). The primary endpoint used will be immediately (1–2 weeks) after the completed intervention.

**Table 2 Tab2:**
[figure not shown]
Participant timeline. Time schedule of enrolment, interventions, and assessments of participants

*ATMS-S* Assessment of Time Management Skills – Swedish version, *SDO-OB* Satisfaction with Daily Occupation – Occupational Balance, *WCPA-SE* Weekly Calendar Planning Activity – Swedish version, *GSE-10* General Self Efficacy Scale 10 items, *DSM-5* The DSM-5 Self-Rated Level 1 Cross-Cutting Symptom Measure-Adult, *ASRS* ADHD Self-report Screening scale, *AQ-short* Adult Autism Spectrum Quotient – short form, *PSOC* Parental Sense of Competence

#### Assessment of Time Management Skills (ATMS-S)

The primary outcome of this trial will be the domain of self-reported time management skills as measured by the Swedish version of the Assessment of Time Management Skills (ATMS-S) questionnaire. The ATMS-S is a self-administered questionnaire with 27 items. Each item is to be answered on a 4-point rating scale. The ATMS-S measures three constructs. The items are thus divided into three subscales, including time management (11 items, the primary outcome), organisation and planning (11 items), and regulation of emotions (5 items). Raw scores from each subscale are transformed into ATMS units, which is a Rasch-based continuous measure ranging from 0 to 100, where a higher value represents better skills [61]. The specific metric used will be change from baseline to completed intervention as the primary point of comparison, and as a secondary comparison change from baseline to 3 months after the completed intervention. The mean/median values will be reported and analysed. The test–retest reliability has been evaluated with good results (the whole scale in the American version had an *r* = 0.89, and for each subscale in the Swedish version, the intraclass correlation coefficient ranged from 0.82 to 0.86) [51, 62].

#### Satisfaction with Daily Occupations – Occupational Balance (SDO-OB)

Occupational balance and satisfaction with daily occupations will be measured by the interview-based questionnaire Satisfaction with Daily Occupations – Occupational Balance (SDO-OB) and measured as change from baseline [63, 64]. The SDO-OB contains 13 items aiming to estimate a person’s satisfaction with their daily activities in the four activity areas of work (3 items), leisure (3 items), domestic tasks (4 items), and self-care occupations (3 items). For each item, the person is asked to answer whether the activity was performed during a given time interval (yes or no). The scores are summed on an activity scale ranging from 0 to 13 activities and data are continuous and will be reported as mean and SD. The level of satisfaction with the performance of each activity is rated on a satisfaction scale from 1 (extremely dissatisfied) to 7 (extremely satisfied). The sum score of satisfaction has a total range of 13 to 91; data are continuous and reported as mean and SD. For each activity area, the participants are asked to rate their perceived occupational balance on a 5-grade scale, ranging from 2 (far too much) to −2 (far too little), which are considered as categorical data and will not be summed but regarded as profiles of occupational balance. These profiles will be categorised and proportions of balance profiles will be compared. Furthermore, the SDO-OB is concluded with two questions regarding global satisfaction with daily occupations and global occupational balance. Global satisfaction with daily occupations is rated from 1 to 5, where 1 indicates the best possible satisfaction with daily occupations. Global occupational balance is rated from 1 to 5, where 1 is far too much engagement in activities and 5 is far too little. Both global scales will be reported as mean and SD in change from baseline. The construct validity of the SDO-OB has been established [64]. The SDO activity and satisfaction scales with 13 items have been shown to have good psychometric properties indicating internal consistency (*α* = 0.83)[65], good validity [63, 65], and good test–retest reliability with *r*_s_ = 0.84 (satisfaction) and *r*_s_ = 0.92 (activity) [66].

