### Consequences of, or issues related to, time management difficulties

Experiences of failure in time management are associated with difficulties in a number of other areas of life. This trial will put the spotlight on occupational balance, regulation of emotions, general self-efficacy, and sense of competence in a parental role. Human occupation has been described in a number of conceptual models as the interplay between the occupation (or activity), the person, and the context [25]. Occupations should be balanced in order to either establish or maintain health. *Occupational balance* is defined as organising daily activities to allow for variation between different types of activities in labour and work, home management, parenting, leisure, and rest activities [26]. In order to establish and maintain occupational balance, time management skills and planning and organisation abilities are important. All activities need to be planned and carried out, taking time into account, which affects the occupational balance over the day, week, and month. Claessens et al. [3] state that time management and organisation skills are essential for maintaining occupational balance, which is crucial for health and well-being and can reduce stress. Occupational imbalance can manifest itself in activity deprivation, which means having only a few recurring daily activities in a limited number of settings [22], thus leading to poor satisfaction with daily life [23]. In others, the imbalance could manifest in far too many activities in a variety of settings, thus leading to extensive problems in managing time, as is often described in persons with ADHD as a result of difficulties in estimating and planning time [15].

Symptoms of inefficient time management, including difficulties in finishing tasks on time and procrastination [27], in people with neurodevelopmental disorders might, beyond executive dysfunction, be related to difficulties in *regulation of emotions* [28]. Emotion regulation involves changes in emotion dynamics and is defined as the process by which we control which emotions we have and how we experience their magnitude, intensity, and duration [29] and how we express them [1, 30]. Emotion regulation changes in structure during the life span from mostly behavioural strategies in childhood to more cognitive strategies in adulthood [31].

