### Statistical analysis plan

#### General statistical considerations

The flow of participants through the study will be illustrated according to the Consolidation Standard of Reporting Trials (CONSORT, Fig. 1) [78].

Prior to data analysis, raw data from each instrument will be coded according to the instructions for the respective instrument. Statistical tests will be two-sided and conducted at the conventional (two-sided) 5% level with no formal adjustment for multiple testing. Secondary outcomes are likely to be highly correlated so that standard adjustment techniques, such as the Bonferroni method, would be conservative [79].

All outcome measures and patient characteristics will be summarised by their trial allocation group and by measurement point. The distribution of outcome data will be examined. The main analysis of outcome data will be the comparison of change from baseline between treatment arms. Change from baseline has a “normalising” effect and standard techniques are generally applicable. To maintain the baseline comparability of the compared groups, the main analyses will be performed on an intention-to-treat basis, meaning that participants will be analysed in the arm they were allocated to. A researcher blinded to group allocation will conduct the statistical analysis, guided by a professional academic statistician (also blinded).

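### Global occupational balance has imbalance at both ends of its scale, so the planned signed change from baseline has no direction that means improvement

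*Protocol article*

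**What the plan says.** The SDO-OB section of the protocol article describes two closing global questions.

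- Satisfaction runs one way: "Global satisfaction with daily occupations is rated from 1 to 5, where 1 indicates the best possible satisfaction with daily occupations".
- Balance runs between two undesirable ends: "Global occupational balance is rated from 1 to 5, where 1 is far too much engagement in activities and 5 is far too little".
- One sentence sets the summary for both: "Both global scales will be reported as mean and SD in change from baseline".

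The same section handles the four area-level balance ratings differently. They run from 2 (too much) to −2 (too little), "which are considered as categorical data and will not be summed but regarded as profiles of occupational balance". Their analysis follows: "These profiles will be categorised and proportions of balance profiles will be compared".

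General statistical considerations makes change the tested quantity: "The main analysis of outcome data will be the comparison of change from baseline between treatment arms". Secondary outcome analysis applies the primary procedure to the secondary outcomes, and Primary outcome analysis defines that procedure as an independent t-test or a Mann–Whitney U-test. Under Objectives, occupational balance is among the outcomes on which LGO-S is hypothesised to be superior to TAU.

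The background section on the consequences of time management difficulties describes imbalance in both directions. One is deprivation: "Occupational imbalance can manifest itself in activity deprivation, which means having only a few recurring daily activities in a limited number of settings". The other is overload: "In others, the imbalance could manifest in far too many activities in a variety of settings".

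**The concern.** A mean change answers a question about improvement only if one end of the scale is better than the other. That is true of global satisfaction but not of global balance. An overloaded participant who reaches balance moves up the scale, and a deprived participant who reaches balance moves down. Both have gained, but their changes have opposite signs and offset each other in the arm mean. A participant who swings from one extreme to the other records the largest possible change with no gain in balance.

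The risk is twofold: a null result on this item when LGO-S does help, or a significant difference whose sign cannot be read as benefit or harm. Choosing Mann–Whitney does not help, because it would rank the same signed changes. The article recognises the problem for the area-level ratings, which have the same two-ended form, but does not carry that handling over to the global item.

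**Working it through.** **Inputs.** The 1 to 5 scale and its end labels, and the change-from-baseline metric, come from the SDO-OB section. The two-sided 5% test comes from General statistical considerations. Two things are not in the article and are assumptions here: that 3 is the balanced category (inferred from the end labels and from the −2 to 2 area scale), and the baseline mix p, the share starting on the too-much side. Because p is not given, a range is shown.

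**The plan's own figure.** The article gives no figure for this item. Its sample size reproduces: d = 8/10 = 0.8, two-sided alpha 0.01 and 80% power give 38.2 by the t-test formula, so 39 per arm; 39/(1 − 0.25) = 52 per arm, 104 in total. It is used below only for the number of completers, 39 per arm.

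**Individual moves.**

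| Move | Signed change | Change in \|score − 3\| |
|---|---|---|
| 1 to 3 (improves) | +2 | −2 |
| 5 to 3 (improves) | −2 | −2 |
| 5 to 1 (no better) | −4 | 0 |

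**Mean change.** If every participant moves k steps towards 3, the mean signed change is k·p − k·(1 − p) = k(2p − 1), and the mean change in distance is −k whatever p is.

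- k = 2, p = 0.5: 2 × 0 = 0, although everyone improves by 2.
- k = 2, p = 0.7: 2 × 0.4 = 0.8, a loss of 1 − 0.8/2 = 60%.
- k = 1, p = 0, 0.25, 0.5, 0.75, 1: −1, −0.5, 0, +0.5, +1.

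**Between arms.** If both arms share the mix p and improve on average by a and b steps, equally on each side, the difference in mean signed change is (2p − 1)(a − b). The true difference is multiplied by 2p − 1, which also sets its sign.

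**Effect on the test.** A simulation used 39 completers per arm, 3,000 replicates and a two-sided 5% t-test. Assumptions: everyone starts out of balance; half of LGO-S and none of TAU improve by one step; random noise of one step up or down, with probability 0.15 each.

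| p | Mean difference, signed | Rejection rate, signed | Rejection rate, \|score − 3\| |
|---|---|---|---|
| 0 | −0.462 | 92.8% | 85.5% |
| 0.1 | −0.377 | 73.5% | 86.3% |
| 0.25 | −0.230 | 32.5% | 86.4% |
| 0.5 | −0.003 | 5.7% | 86.2% |
| 0.75 | +0.235 | 34.2% | 86.5% |
| 0.9 | +0.370 | 71.8% | 85.4% |
| 1 | +0.462 | 92.5% | 85.7% |

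At an even mix the signed test rejects at about its nominal 5% despite a real benefit. The same benefit appears as a negative difference at p = 0 and a positive one at p = 1.

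**The case against.** The strongest objection concerns scope. A reader might infer that the trial cannot test its occupational-balance hypothesis at all. The documents do not support that: the area-level ratings are kept as profiles and compared as proportions, and that analysis does not cancel opposite movements. The defect is confined to the global item.

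A reader might also infer that the loss will be severe. That depends on a baseline mix the article does not give. The background says that imbalance can go either way, which makes a mixed sample foreseeable, but it is a summary of literature and gives no proportions for these participants. With a one-sided sample nothing cancels, and in the simulation the signed test then rejects somewhat more often than the distance measure (about 93% against 86%). Both of these limits stand.

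Two further objections carry less weight. First, raw data are to be coded by each instrument's instructions, which might re-centre the item. The article states a 1 to 5 range with labelled ends and mentions no re-centring, so this is only a possibility. Second, the quoted sentence is about reporting. That is so, but the general and secondary-outcome analysis rules make the between-arm comparison of change the test, so the signed metric does not remain descriptive.

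**Conclusion.** The point holds for the global balance item. As written, the item is summarised and tested as a signed change on a two-ended scale, which has no direction of improvement, so the result cannot validly support the claim that LGO-S improves occupational balance more than TAU. If improvement is equal on both sides, the effect is scaled by 2p − 1: lost completely at 50/50, reduced by 60% at 70/30, and undiminished if all start on one side, although its sign then depends on that side. These sizes are illustrations over an unknown mix and take 3 as the balanced category. The choice of metric is wrong even where nothing cancels.

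The point reaches no further. Mean change is sound for global satisfaction, the area-level analysis stands, and the primary outcome and sample size are unaffected. This is a secondary-outcome issue that should be corrected, not one that endangers the trial's main result.

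**What to change.** For the global balance item only, replace the signed change with one of two measures, chosen before allocation is revealed to the analysts:

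- the change from baseline in |score − 3| (0 best, 2 worst), compared between arms under the existing procedure; or
- the proportion rating themselves in balance, compared between arms, in line with the categorical handling of the area-level items.

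Confirm from the instrument that 3 is the balanced category, and state it. Report the direction of imbalance (too much, balanced, too little) descriptively by arm and time point, because the distance measure hides it. Leave global satisfaction as mean change.

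The cost is a recode of one variable already being collected and one sentence in the analysis plan. No new data, participants or assessments are needed.

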#### Weekly Calendar Planning Activity (WCPA-SE)

Executive functioning will be measured with the Swedish version of the Weekly Calendar Planning Activity (WCPA-SE) [67]. The WCPA-SE measures a person’s ability to coordinate and integrate different aspects of executive functioning, such as organisation and planning, inhibition of distractions, monitoring the passage of time, and strategies used in a cognitively challenging planning task [68]. When administering the WCPA-SE, the person is given a list of 17 appointments and meetings to be entered into a blank weekly calendar. The test is timed, with five rules to adhere to, and the strategies used by the person are noted by the test leader. The WCPA-SE has three difficulty levels. In this trial, level 2 will be used. A recent study has shown that the test–retest reliability between two tests was weak, but when repeated, the reliability between tests two and three was acceptable to excellent (ICC = 0.65–0.91) [69]. Thus, to reduce random variation and possible learning effects, two alternative lists of appointments will be used along with two baseline tests, first at enrolment and then at the time of the other baseline assessments. The second assessment will be used as the baseline assessment [69]. The outcomes used in this trial will be the total number of correctly entered appointments, the total time to complete the task, the number of rules followed, the number of strategies used, and the efficiency score [67]. All these outcomes are continuous data and will be reported as mean (SD) as change from baseline.

#### General Self-Efficacy Scale (GSE-10)

Self-efficacy will be measured with the Swedish version of the General Self Efficacy Scale (GSES-10). The GSES-10 has 10 items that are scored on a 4-point rating scale. The GSES-10 measures self-rated belief in personal competence to effectively deal with a range of stressful situations and is reported with a continuous score range of 10–40. Higher scores indicate better self-efficacy and will be reported as mean (SD). The GSE-10 has been translated into 26 languages and has been used internationally and has shown good validity and reliability [70].

#### Symptom scales

Three scales will be used to monitor psychiatric symptoms. The first scale will be the DSM-5 Self-Rated Level 1 Cross-Cutting Symptom Measure-Adult in Swedish, with 23 items in 13 domains of mental health. Participants report a self-rated measure of recent symptoms rated from none (0) to severe (4) [71]. Scores will be summed by domain and presented as mean (SD). The second scale used will be the World Health Organization adult ADHD self-report screening scale (ASRS). This is an 18-item ADHD symptom questionnaire scored on a 5-point rating scale from never to very often and intended for use in the general population [72]. The first six items have shown to be predictive of ADHD and will be summed and reported as continuous data using mean (SD). The third scale used will be the Swedish version of the Adult Autism Spectrum Quotient (AQ-short), which is used to monitor autism symptoms. This scale includes 28 statements with four possible responses from definitely disagree (1) to definitely agree (4) [73] and will be scored according to a specific scoring key provided by the instrument developer. Scores will be reported as continuous and as mean (SD).

#### Cost-effectiveness measure

To enable a cost-utility analysis, we will measure health-related quality of life using the EQ-5D-5L, developed by EuroQol [74]. In the EQ-5D-5L, the individual’s health status is measured in the five dimensions of mobility, self-care, usual activities, pain/discomfort, and anxiety/depression using a 5-level scale ranging from no problem to extreme problems. By using a value set, this can be converted to a health index ranging from 0 (dead) to 1 (perfect health). A Swedish value set is currently under development and if available will be used when analysing the data. By multiplying the change in health-related quality of life by the duration of this change, expressed in years, the result will be the change in quality-adjusted life years (QALYs), which is the outcome most commonly used in health economic evaluations.

#### Parental Sense of Competence

Participants with children living at home will be administered the Parental Sense of Competence Scale (PSOC) to measure the domain of self-efficacy in the parental role. The PSOC is a self-rated questionnaire with 15 items rated on a 6-point rating scale from 1 (strongly agree) to 6 (strongly disagree) that measures parents’ perceptions of their parental skills [75]. The PSOC, used in the general population, measures three factors—satisfaction, efficacy, and interest [76], and as sum will be calculated for each factor which will be reported as continuous and mean (SD). The PSOC has previously been used in assessing parents with ADHD [77] and people with mental and neurodevelopmental disabilities [13].

#### Trial-specific forms

Two trial-specific demographic forms will be collected only at pre-intervention. One form will be filled out by the participant with their information, including age, sex, family status, living arrangements, and information on education and work. The second form will be filled out by the recruiting staff and contains information on diagnosis, medication, length of contact with the services, and any prior prescribed time-assistive devices and contacts with an occupational therapist. In the case of dropouts, the time of occurrence will be noted, along with the reason if given by the participant.

To evaluate the process of implementing the interventions, a form will be filled out for each participant by the interventionist. For participants receiving the LGO-S intervention, the form will document the number of sessions, as well as which sessions they attended. For participants receiving TAU, the form will document the number of sessions, the time duration per session, the content of any interventions, and prescribed and/or recommended cognitive assistive devices.

### Sample size

A total of 104 participants will be recruited for the trial. There will be 52 participants in each group. The sample size calculation is based on the earlier feasibility study showing that an increase of 8 ATMS units in mean difference (SD = 10 for both groups) on the time management subscale of the ATMS-S was considered a significant effect [52]. Furthermore, the calculation took into account an 80% power to detect change, a dropout rate of 25%, and a statistical significance level of *p* < 0.01.

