The LGO intervention has been translated and adapted to a Swedish context and is called LGO-S [52]. LGO-S is intended for use in clinical settings for people with neurodevelopmental or mental disorders or mild intellectual disability [53]. A feasibility study of LGO-S was performed in Swedish open psychiatric clinics with 75 participants with mental and/or neurodevelopmental disorders (dropouts *n* = 20) [52]. The results showed significant improvements in time management, organisation and planning, and regulation of emotions. These improvements were retained in both the 3-month and 12-month follow-ups [52, 54]. Furthermore, the number of activities the participants performed in their daily life and their satisfaction with these activities improved significantly during the study, as well as some aspects of executive functioning [52]. A qualitative interview study with participants in the LGO-S intervention rendered rich descriptions of how they had managed to increase the structure in their daily life and to accomplish more tasks. The participants also indicated an increase in self-efficacy in relation to planning and time management and the experienced impact of belonging to a group [55]. In order to establish to what extent the improvements highlighted in the feasibility study are due to LGO-S and have an effect over and above usual treatment, a randomised controlled trial is needed.

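### The trial is sized at alpha 0.01 but tested at two-sided 5%, so the stated 80% power is not that of the planned test, and no between-arm basis is shown for the 8-unit difference

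*Protocol article*

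**What the plan says.** All references are to the protocol article.

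- **Sample size**, enrolment: "A total of 104 participants will be recruited for the trial. There will be 52 participants in each group".
- **Sample size**, effect: "The sample size calculation is based on the earlier feasibility study", with the effect given as "an increase of 8 ATMS units in mean difference (SD = 10 for both groups" on the time management subscale. The text adds that such an increase was regarded as a significant effect.
- **Sample size**, error rates and attrition: "80% power to detect change, a dropout rate of 25%, and a statistical significance level of *p* < 0.01". Sidedness is not given there.
- **General statistical considerations**: "Statistical tests will be two-sided and conducted at the conventional (two-sided) 5% level with no formal adjustment for multiple testing".
- **Primary outcome analysis**: change from baseline is compared between LGO-S and usual treatment by an independent t-test or a Mann–Whitney U-test. No separate significance level is set.
- **Interventions to improve time management** (Background): the feasibility study is described as 75 LGO-S participants with 20 dropouts, whose skills improved and held at follow-up. No comparator is mentioned. To learn whether the improvements "have an effect over and above usual treatment, a randomised controlled trial is needed".
- **Individual occupational therapy (TAU)**: the control arm receives individual therapy directed at time management, organisation and planning.

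**The concern.** Two inputs to the power statement do not match the test that will be run.

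First, the alpha in the sample size is not the alpha in the analysis, and the article does not say why. The 80% then belongs to a test at 0.01 that the analysis section does not plan. A reader cannot tell from the article what power the planned test has, or what difference the trial can detect.

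Second, the primary analysis is a contrast between two active treatments. The 8 units come from a study of one of them, and the article itself says that study left the effect beyond usual treatment open. If 8 is the gain seen within LGO-S participants, entering it as the between-arm difference assumes that individual occupational therapy produces no gain on the same skills. A null result could then be read as evidence of no added benefit from a well-powered trial, when the power applied only to a large contrast.

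**Working it through.** **Inputs** (all from Sample size unless noted): difference 8 units; SD 10 in each group; power 0.80; alpha 0.01; dropout 25%; 52 per arm, 104 in total. Allocation is 1:1 (Trial design). Analysis alpha is 0.05, two-sided (General statistical considerations). Standardised difference d = 8/10 = 0.8.

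**1. Reproduce the stated figure.** The normal approximation per arm is n = 2(z₁₋α/₂ + z₁₋β)²/d². At two-sided 0.01 this is 2(2.576 + 0.842)²/0.64 = 36.5, so 37 per arm. Solving the two-sample t-test exactly (noncentral t) gives 38.2, so 39 per arm. Allowing for dropout, 39/0.75 = 52 per arm, and 2 × 52 = 104. The match is exact.

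Other readings of alpha at 80% power do not give 52 per arm (t-test, after dropout):

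| Alpha | Evaluable per arm | Randomised per arm |
|---|---|---|
| 0.01 two-sided | 39 | 52 |
| 0.01 one-sided | 33 | 44 |
| 0.05 two-sided | 26 | 35 |
| 0.05 one-sided | 21 | 28 |

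So 0.01 was the value used, two-sided, and 8 was entered as the between-arm difference.

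**2. Repeat at the analysis alpha.** Two-sided 0.05 with d = 0.8 and 80% power gives 25.5, so 26 evaluable per arm. Then 26/0.75 = 34.7, so 35 per arm, or 70 randomised in total.

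**3. Power of the planned test.** With 39 evaluable per arm and a difference of 8, power is 93.7% at two-sided 0.05 and 81.0% at two-sided 0.01.

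**4. Difference detectable with 80% power**, 39 evaluable per arm, SD 10: 6.4 units at 0.05 and 7.9 units at 0.01.

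**5. Power for smaller differences.** The document gives no estimate of the gain under usual treatment, so the differences below 8 are assumptions that show the range (39 evaluable per arm, SD 10, t-test).

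| Between-arm difference | Power at 0.05 | Power at 0.01 |
|---|---|---|
| 8 | 94% | 81% |
| 7 | 86% | 67% |
| 6 | 74% | 51% |
| 5 | 59% | 34% |
| 4 | 41% | 20% |

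**6. Basis of the 8 units.** Three statements have to be read together. Sample size takes 8 units from the feasibility study. The Background describes that study without a comparator and leaves the effect over usual treatment for this trial to establish. The TAU section describes a comparator aimed at the same skills. Nothing in the article supplies an LGO-S versus usual treatment difference from which 8 could be drawn.

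**The case against.** **The sizing alpha is a planning input, not a decision rule.** A reader might infer that the primary test has two success thresholds, so that a p-value between 0.01 and 0.05 would be both negative and positive. The article does not support that. Only General statistical considerations says how tests are conducted, and the primary analysis section sets no other level. The test level is 5%. What stands is that the power statement was computed for a different level, without explanation.

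**The mismatch is conservative.** Sizing at a stricter alpha than the test makes the trial larger than 80% power at 8 units requires (104 against 70). This stands in full. The alpha difference alone does not leave the trial short of power.

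**The 8 units may not be a pre-post change.** It is tempting to state that 8 is a single-arm, within-group gain. That is a reasonable inference, but the article never calls the feasibility study single-arm and does not report its change in ATMS units. The phrases about a mean difference, an SD for both groups and an effect regarded as significant would also fit a planning threshold. The cited study is not at hand. What stands is narrower: the article shows no between-arm basis for the figure.

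**A serious power shortfall is not shown.** A reader might conclude that power for the true contrast is far below 80%. The differences of 4 to 7 units are assumptions. At the 5% level power stays at or above 80% down to 6.4 units, and is still 74% at 6.

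**Conclusion.** The point holds in two parts that pull in opposite directions.

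The alpha inconsistency is firm. The sample size was computed at two-sided 0.01 and the tests are planned at two-sided 5%, so 80% is not the power of the planned test. For the article's own 8 units and SD of 10, that power is about 94%. The calculation itself contains no arithmetic error.

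The lack of a between-arm justification for 8 units is also firm, but its effect on power cannot be computed from the article. If 8 is a within-group gain, using it as the contrast assumes no gain under usual treatment. The spare power from the stricter sizing alpha absorbs part of any optimism: at 5%, power falls below 80% only if the true difference is under about 6.4 units.

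These figures assume an SD of 10 for the change score in each arm, 39 evaluable participants per arm (exactly 25% dropout) and the t-test. The article does not say what the SD of 10 is an SD of.

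**What to change.** 1. Use one alpha for the primary comparison in both sections: two-sided 0.05, as General statistical considerations already states.
2. Keep 104 and restate the power: 39 evaluable participants per arm give 80% power for a between-arm difference of 6.4 ATMS units, assuming an SD of 10. Mention that enrolment was originally computed at two-sided 0.01 for 8 units.
3. State what the 8 units represent (observed change within LGO-S participants, a difference between groups, or a threshold chosen for planning) and whether the SD of 10 refers to change scores or to scores at one time point.
4. Add power at the 5% level for smaller assumed differences: 86% at 7 units, 74% at 6, 59% at 5 and 41% at 4, labelled as assumptions.

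The cost is a few sentences in the protocol and the registry entry. Enrolment and the planned test do not change. The downside is that the power statement looks less favourable if the true difference is below 6.4 units. The article reports 75 of 104 recruited in April 2021, so on that status the correction could be made before the final analysis.
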